### Sample size justification

Approximately 6% of women will achieve smoking cessation with individual behavioural support via a structured intervention during pregnancy [10]. Previous large-scale trials in the UK have used a figure of 9% cessation in pregnancy unaided, with a further 6% cessation arising from an intervention [11]. Longitudinal data on pregnancy in women who quit after the first antenatal visit and before late pregnancy gives a similar figure (14.6%) [10]. We aim to double the ‘routine care’ cessation rate of 9% to give an intervention cessation rate of 18%. In terms of creating a model of care for pregnant smokers, we feel it is important to have a substantial increase in cessation rates over routine care to make it a viable clinic. Assuming a 5% level of statistical significance and 80% statistical power, the sample size is 225 per study arm. In a sensitivity analysis, under the assumption of no dropouts, the trial would have higher statistical power of precisely 90% or alternatively allow detection of a lower cessation rate of 16% in those randomised to the smoking cessation clinic.

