### Randomisation

Patients are randomised on a secure data spreadsheet using a computer-generated random allocation list with allocation concealment. We are utilising block randomisation (block size of 4) with stratification for age, parity, and history of previous fetal growth restriction (see Fig. 1: trial schema).

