## Analyses

### Statistical analysis

Outcomes in the smoking cessation intervention group will be compared to those for all control patients in an intention-to-treat analysis. A 5% level of significance will be used in a chi-square test for a difference in overall smoking cessation rates. Post hoc testing will consist of comparing the two control groups, i.e. controls under routine care versus controls with third trimester study scans (screening for IUGR). In a secondary analysis, IUGR rates will be compared between the smoking cessation group and the control group screened for IUGR. An analysis of covariance (ANCOVA) analysis will be used to adjust for the stratification factors (age, parity, and history of fetal growth restriction). Intervention adherence will be assessed, and the group comparisons will be reproduced in a per-protocol population. Potential patient selection bias will be assessed using the Berger-Exner test. Statistical analysis will be performed using the STATA IC15 statistical package.

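### The primary cessation test leaves out the factors used to stratify randomisation, and the only adjusted method named, ANCOVA, is not tied to any outcome; a stratified binary analysis would be a free improvement

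*Protocol article*

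**What the plan says.** **Design.** The Randomisation section of the protocol article specifies "block randomisation (block size of 4) with stratification for age, parity, and history of previous fetal growth restriction".

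**Primary test.** The Statistical analysis section says: "Outcomes in the smoking cessation intervention group will be compared to those for all control patients in an intention-to-treat analysis". It continues: "A 5% level of significance will be used in a chi-square test for a difference in overall smoking cessation rates". The primary outcome is validated abstinence up to the end of pregnancy, so each woman is a success or a failure.

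**Adjustment.** The same paragraph then names a control-versus-control comparison and a comparison of IUGR rates. After these it says that an ANCOVA "analysis will be used to adjust for the stratification factors (age, parity, and history of fetal growth restriction"). The sentence names no outcome. No Mantel-Haenszel, logistic or other binary-outcome model appears in the article.

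**Sample size.** The Sample size justification targets 9% versus 18% and states: "Assuming a 5% level of statistical significance and 80% statistical power, the sample size is 225 per study arm".

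**The concern.** Balancing allocation within strata removes chance differences between arms in the stratifying factors. An unstratified chi-square does not use this. Its variance still contains the between-stratum spread in quit rates, although the design has taken that spread out of the treatment comparison. If the factors predict quitting, the standard error is a little too large, the true type I error falls below 5%, and some power is given away.

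The adjustment sentence adds an ambiguity. If ANCOVA is meant for cessation and IUGR, it is an unconventional choice for yes/no outcomes. If it is meant only for continuous outcomes, the primary endpoint has no stated analysis that uses the stratification factors. Either way the wording needs settling before the data are analysed, so that the choice of model cannot depend on the result.

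**Working it through.** **1. Reproduce the plan's figure.** Inputs from the Sample size justification: 9% versus 18%, 5% significance, 80% power. Sidedness is not stated; two-sided is assumed, with no continuity correction.

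n = [1.960 × √(2 × 0.135 × 0.865) + 0.8416 × √(0.09 × 0.91 + 0.18 × 0.82)]² / 0.09²
= [1.960 × 0.4833 + 0.8416 × 0.4791]² / 0.0081 = 225.1, that is 226 per arm.

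Power at 225 per arm is 79.98%. The stated 225 therefore belongs to the unadjusted chi-square, with nothing in hand. The article also says that "under the assumption of no dropouts, the trial would have higher statistical power of precisely 90"%. That is a separate matter, but 225 per arm with complete follow-up already gives only 80.0%.

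**2. Why the chi-square can be conservative.** Let quit rates p_s vary over strata with mean p. The chi-square uses variance p(1 − p). With balance inside strata, only p(1 − p) − Var(p_s) applies. The ratio of true to assumed variance is

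R = 1 − Var(p_s) / [p(1 − p)], and the actual level is 2Φ(−1.960/√R).

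The article gives no stratum effects, so these are assumed. Take odds ratios for quitting of 3 (age), 0.33 (parity) and 0.5 (previous growth restriction). Assume half the women in each age group, 60% parous, and a growth-restriction history in 15% of parous women only. At an overall 9%, the stratum rates and shares are:

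- 8.3% (share 0.20), 2.9% (0.255), 1.5% (0.045)
- 21.3% (0.20), 8.2% (0.255), 4.3% (0.045)

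Var(p_s) = 0.0044, so R = 1 − 0.0044/0.0819 = 0.947, and the level is 2Φ(−1.960/0.973) = 4.4%.

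**3. Size of the effect by simulation.** 6,000 trials per row, N = 450, blocks of 4 within strata, overall rates 9% versus 18%, same assumed strata shares.

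| Assumed odds ratios (age / parity / previous growth restriction) | Power: chi-square | Power: Mantel-Haenszel | Power: logistic | Power: ANCOVA | Type I: chi-square | Type I: Mantel-Haenszel |
|---|---|---|---|---|---|---|
| 1 / 1 / 1 | 81.0% | 80.8% | 80.5% | 80.8% | 5.2% | 5.2% |
| 1.5 / 0.67 / 1 | 80.5% | 80.7% | 80.4% | 80.7% | 4.8% | 4.8% |
| 2 / 0.5 / 0.7 | 81.1% | 81.7% | 81.4% | 81.7% | 4.1% | 4.2% |
| 3 / 0.33 / 0.5 | 81.5% | 83.2% | 83.0% | 83.0% | 4.1% | 4.7% |

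The Monte Carlo error of the type I figures is about 0.3 points. In the third row the stratified test is also low, so most of that shortfall is simulation noise. The largest gain from stratifying is 83.17 − 81.53 = 1.6 points. ANCOVA fitted to the 0/1 outcome had type I error of 4.2 to 5.2% and power within 0.4 points of logistic regression.

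**4. Which outcome ANCOVA serves.** The two outcomes named before the ANCOVA sentence, cessation and IUGR, are both rates. The outcome list also contains birth weight, estimated fetal weight and length of stay, for which ANCOVA is a normal choice. The text does not decide between these readings.

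**The case against.** The case for leaving the text alone is substantial. The chi-square is a valid test, it is the one the sample size was built on, and the planned power does not rely on any gain from stratification. The strata are not ignored altogether, since an adjusted analysis is planned. Model form by outcome is commonly left to an analysis plan, and this is a condensed article. All of this stands as a limit on the importance of the point. It does not remove it: the article itself fixes an unstratified primary test for a stratified design, and it chooses the one adjusted method it names.

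Three stronger readings are tempting, and the documents do not support them.

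- **ANCOVA is wrongly applied to the yes/no endpoint and the result is mis-specified.** The sentence names no outcome. Even if cessation were meant, a linear model on a 0/1 outcome estimates an adjusted risk difference, and it kept its level in the check above. The fault is unclear wording, not an invalid result.
- **Power is seriously lost.** Losses of about 4 points can be produced (70.4% versus 74.3%), but only by letting control quit rates run from 1% to 23% over four strata. That is an odds ratio between extremes of (0.23/0.77)/(0.01/0.99), about 30. Nothing in the article suggests effects of that size. The low power in that scenario is also mostly not the chi-square's doing: a fixed odds ratio within strata gives a smaller overall difference, which lowers both tests.
- **Constant variance gives wrong standard errors because the arms are unequal.** Cessation is compared in about 225 versus 226 women. There the ratio of constant-variance to unequal-variance standard error at 18% and 9% is √(0.001017/0.001018), about 1.00. The only comparison of about 225 with 113 that the plan makes is for IUGR. No IUGR rates are given, so neither the size nor the direction of any error can be stated.

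**Conclusion.** The point holds as a low-cost improvement in specification, not as an error that threatens the trial. The primary test is valid and protects the type I error. It is slightly conservative only if the stratification factors predict quitting, with a level of about 4 to 5%. The power given up is about 0 to 1.6 points, and nil if the factors are weak. These sizes rest on assumed stratum shares and odds ratios, with overall rates held at 9% and 18%; the article gives no such figures. What is firmly established from the text is that the analysis named as primary does not reflect the randomisation, that ANCOVA is not tied to an outcome, and that no adjusted analysis suited to a binary outcome is named.

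**What to change.** - **Primary analysis.** Use a Mantel-Haenszel test of cessation, intervention versus all controls, stratified by age, parity and previous growth restriction as used in randomisation. Alternatively, use a logistic regression including those factors, reported as a marginal risk difference with 95% CI. State that this is the primary analysis.
- **Sensitivity analysis.** Keep the simple chi-square, which preserves the link to the sample size calculation.
- **Other binary outcomes.** Use the same approach for IUGR and the remaining yes/no outcomes.
- **ANCOVA.** Limit it to continuous outcomes such as birth weight, and name them.

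The cost is a change of wording. No new data are needed, because the stratification factors are already recorded for every randomised woman. If the factors turn out not to be prognostic, the check above shows a difference of 0.2 points for Mantel-Haenszel (81.0% versus 80.8%) and 0.5 points for logistic regression (81.0% versus 80.5%).

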**Methods:**

This is a pragmatic randomised controlled trial of a dedicated smoking cessation clinic versus routine antenatal care as an intervention to reduce cigarette smoking behaviour. Smoking mothers randomised to the Smoking cessation Through Optimisation of clinical care in Pregnancy (STOP) clinic will have all antenatal care provided by a team comprising an obstetrician, a midwife, and a smoking cessation practitioner. This intervention includes ultrasound screening for fetal growth restriction. The control arm comprises two groups: one receiving standard care with ultrasound screening for fetal growth restriction, and one receiving standard care with ultrasound screening for growth restriction only if clinically indicated by their healthcare provider. Four hundred and fifty women will be recruited and randomised to either intervention or control arms stratifying for age, parity, and history of fetal growth restriction.

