### Controls

The control group is 226 patients booked and recruited at the same time and randomised to ‘routine care.’ These patients have smoking cessation advice given as a ‘once-off’ at the booking visit via verbal or written information on the HSE Quit service, which is the current routine care in the Coombe and all obstetric units in Ireland [17]. The patients will attend either a general obstetric clinic or midwifery-led clinic and have a booking scan and 20–22-week anomaly scan as normal. The control group will be divided into two groups: 113 will have an additional scan at 32 and 36 weeks to screen for intrauterine growth restriction (IUGR), and 113 will receive no additional scans unless clinically indicated by their team. This is done to ensure testing of the hypothesis that the clinic as the intervention is responsible for any difference in outcomes, rather than the provision of additional ultrasound scans.

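### The controls are split to separate the clinic from its extra scans, but the direct contrast (STOP v scanned controls) is planned only for IUGR, not for smoking cessation

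*Protocol article*

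**What the plan says.** The abstract of the protocol article makes growth scanning part of what STOP women receive: "This intervention includes ultrasound screening for fetal growth restriction". The Ultrasound section places these scans at 32 and 36 weeks.

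The Controls section divides the comparison arm: "113 will have an additional scan at 32 and 36 weeks to screen for intrauterine growth restriction (IUGR), and 113 will receive no additional scans". It gives one reason for doing so, namely "testing of the hypothesis that the clinic as the intervention is responsible for any difference in outcomes, rather than the provision of additional ultrasound scans".

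The Statistical analysis section then fixes three between-group comparisons:

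1. STOP v pooled controls: "Outcomes in the smoking cessation intervention group will be compared to those for all control patients", with a chi-square test on cessation at the 5% level.
2. Control v control: "Post hoc testing will consist of comparing the two control groups, i.e. controls under routine care versus controls with third trimester study scans". The outcome is not named.
3. STOP v scanned controls, as a secondary analysis of one outcome: "IUGR rates will be compared between the smoking cessation group and the control group screened for IUGR".

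The covariate-adjusted analysis and the per-protocol repeat reuse these groupings and add no further contrast.

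**The concern.** STOP v scanned controls is the one comparison in which both sides are assigned the third-trimester scans, so it isolates the clinic. The Controls section sets up the split to support attribution for any outcome, yet the analysis section uses this contrast for growth restriction alone. Smoking cessation, the primary outcome, lacks the comparison that the split was built to provide.

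What is at stake is attribution. If STOP beats pooled controls on cessation, the plan names no direct analysis to support the statement that the clinic rather than the scans was responsible. The same gap affects secondary outcomes on which a scan finding could act more directly: induction, iatrogenic pre-term birth and mode of delivery. Because the analysis section spells out its comparisons, this is a mismatch between two stated parts of the protocol and not merely a detail left to a later document.

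**Working it through.** **Inputs.** Cessation 9% under routine care and 18% in STOP, 5% significance, 80% power, 225 per arm (Sample size justification). Control arm 226, split 113/113 (Controls). Sidedness is not stated; two-sided is assumed. No dropout rate is given; the main figures assume none.

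**Formulas.** For groups of size n1 and n2 with rates p1 and p2, let p̄ be the size-weighted mean rate, and

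- SE0 = √[p̄(1−p̄)(1/n1+1/n2)]
- SE1 = √[p1(1−p1)/n1 + p2(1−p2)/n2]
- power = Φ[(|p1−p2| − 1.96·SE0)/SE1]
- 95% CI half-width = 1.96·SE1

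**The plan's own figure.** 225 v 225, 9% v 18%: p̄ = 0.135, SE0 = 0.0322, SE1 = 0.0319, giving Φ(0.84) = 80.0%. The stated 225 per arm reproduces.

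**What each contrast estimates.** Let U be the rate in unscanned controls, S = U + s in scanned controls, and U + c + s in STOP, where c is the clinic effect and s the scan effect, taken as additive.

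- STOP − all controls = (U + c + s) − (U + s/2) = c + s/2
- Scanned − unscanned controls = s
- STOP − scanned controls = c

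**The control v control comparison** (113 v 113, starting from 9%):

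| Rate in scanned controls | SE0 | SE1 | Power |
|---|---|---|---|
| 12% | 0.0408 | 0.0407 | 11% |
| 15% | 0.0432 | 0.0430 | 28% |
| 18% | 0.0455 | 0.0451 | 51% |
| about 22.5% | 0.0485 | 0.0476 | 80% |

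With 9% in both halves, the half-width is 1.96·√(2×0.09×0.91/113) = 0.0746, or about 7.5 points, against a target effect of 18 − 9 = 9 points.

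**The contrast not planned for cessation** (225 STOP v 113 scanned controls, 18% v 9%): p̄ = 0.150, SE0 = 0.0412, SE1 = 0.0372, so power = Φ[(0.09 − 1.96×0.0412)/0.0372] = Φ(0.25), about 60%. The half-width is 1.96×0.0372 = 0.073, or about 7.3 points. With an assumed 10% dropout, power is about 55%; with 20%, about 50%.

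**Timing.** The primary outcome is continuous abstinence from a quit date no later than 28 weeks (Primary outcome section). The added scans are at 32 and 36 weeks. They therefore follow every permitted quit date and cannot start a qualifying quit. They could act only by changing late relapse or by changing how abstinence is ascertained. The Conclusions section says many women relapse before the end of pregnancy, so s need not be zero, but the route is narrow.

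**The case against.** **The planned comparisons already contain the answer.** A reader might infer that comparing the control halves cannot address the question at all. That is too strong. With equal halves, STOP − scanned = (STOP − all controls) − ½(scanned − unscanned). This is an identity, so for any outcome on which both planned comparisons are reported, the direct contrast can be derived. The objection stands this far: the gap is an unnamed contrast, not an unanswerable question. However, the control v control test has no named outcome and is labelled post hoc, and the plan does not say that the two results will be combined.

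**The pooled comparison is legitimate.** The clinic is offered as a package that includes scans, in a pragmatic trial, and STOP v all controls is a randomised comparison of that package with the control arm. This stands. Nothing here invalidates the primary test, and calling the delivery outcomes confounded would misdescribe a package effect.

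**A scan effect on cessation is unlikely to be large.** This largely stands, on the timing above. It does not cover delivery outcomes, which scan findings can influence directly.

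**Two further inferences the text does not support.** One is that scanned controls have carbon monoxide and cotinine measured at their scans: those measurements are described under the intervention, and the Controls section mentions only the scans. The other is that a non-significant control v control result will be read as showing no scan effect: the protocol states no such rule.

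**The direct contrast is hardly more precise** (7.3 v 7.5 points). True, but it estimates the clinic effect itself, whereas the control comparison estimates only the scan effect.

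**Extra secondary contrasts can be left to an analysis plan.** Often so. Here the article itself lists which contrast goes with which purpose, and the list does not match the reason given for the split.

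**Conclusion.** The point holds as a mismatch of moderate severity. The control arm is split so that outcome differences can be attributed to the clinic, but the scan-balanced contrast is planned only for growth restriction. For cessation, the pooled comparison gives c + s/2 under additivity. The control comparison informs s only weakly: about 11% power for a 3-point effect, about 51% for one as large as the whole 9-point target, and a half-width of about 7.5 points.

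A reader might conclude that the primary analysis is unsound. The documents do not support that: it remains a valid test of the package, and any scan effect on the primary outcome is probably modest. The exposure is greater for induction, iatrogenic pre-term birth and mode of delivery.

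The figures assume two-sided testing, the normal approximation without continuity correction, no dropout, the protocol's 9% and 18%, and STOP women receiving the 32- and 36-week scans as the Ultrasound section says. The Clinic structure section limits fetal biometry to clinical indication, so these two sections should be reconciled.

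**What to change.** - Keep STOP v all controls as the primary test, described as a test of the clinic package.
- Before group-level data are seen, pre-specify STOP v scanned controls as a named secondary contrast on validated cessation and on induction, iatrogenic pre-term birth and mode of delivery. Report each as a risk difference with 95% CI.
- Rest any statement that the clinic rather than scanning is responsible on that contrast.
- Name the outcomes for control v control. Report it as a supportive estimate with CI, and say that a non-significant result is not evidence of no scan effect.

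The cost is some analysis wording and one added contrast, with no new participants or data. The downside to state openly is limited power: about 60% for 18% v 9% with 225 v 113, half-width about 7.3 points, before dropout. The contrast should therefore be read as an estimate and not as a second confirmatory test. If it is added after group-level results are known, it would itself be post hoc.

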### Population

This trial aims to recruit women who self-report smoking at least one cigarette per day and do not have any comorbidities requiring specialist antenatal care. The inclusion and exclusion criteria are detailed in Table 1.

**Table 1 Tab1:** Eligibility criteria

Inclusion criteria:	
1	≥ 18 years old
2	Singleton pregnancy
3	Smoking ≥1 cigarette daily
4	English language spoken
Exclusion criteria:	
1	Significant maternal medical disorder, e.g. cardiac, haematological, or endocrine disease requiring specialised maternal antenatal care
2	Significant maternal psychiatric disorder, e.g. delusional or psychotic disorders, severe depression requiring hospitalisation, use of ≥ 2 psychotropic drugs for treatment
3	Serious comorbid addiction issues, e.g. opiate abuse, methadone maintenance program
4	Positive serology requiring specialised antenatal care
5	Significant fetal anomaly defined as aneuploidy, life-limiting, or lethal fetal anomaly
6	Intellectual disability or lack of capacity
7	Poor or no understanding of the English language

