### Intervention

#### Study protocol

Patients in the STOP clinic have their booking visit between 10 and 19 weeks and see the obstetric team, midwife, and smoking cessation practitioner. Baseline demographics, educational level attained, health literacy, previous quit attempts, and motivation are assessed with a behavioural questionnaire. Data on the patient’s current smoking status and habits, including the use of other tobacco products and e-cigarettes, will be recorded and a measure of her level of addiction will be performed via the Fagerström test [12].

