### Primary outcome

The Russell Standard for reporting of smoking cessation in clinical trials will be followed [16].

The primary outcome is self-reported, continuous abstinence from smoking between the quit date and end of pregnancy, validated by exhaled CO or urinary cotinine. The quit date is targeted as being at or before 16 weeks’ gestation and no further than 28 weeks’ gestation.

Secondary outcomes are (see Additional file 1):
*Smoking*. Number of cigarettes smoked. Smoking cessation at 3 months post quit date, 6 months post quit date and/or end of pregnancy. Smoking cessation at 6 months postpartum*Psychological*. Urge to smoke, tobacco withdrawal symptoms, self-confidence in stopping smoking, self-reported depression at end of pregnancy*Fetal morbidity and mortality including neonatal measures*. Miscarriage, stillbirth, neonatal death, birth weight, estimated fetal weight at 32 weeks, estimated fetal weight at 36 weeks, spontaneous pre-term birth, iatrogenic pre-term birth, birth injury, neonatal complication, oxygen dependence, admission to neonatal unit, length of stay of neonate. Modified from Core Outcome Measures in Effectiveness Trials (COMET) Initiative [18]*Maternal morbidity and mortality including delivery outcomes*. Maternal death, mode of delivery, need for induction/delivery, maternal need for intensive care, maternal length of stay, pre-eclampsia, pregnancy-induced hypertension, postpartum haemorrhage, blood transfusion, late maternal complication. Modified from COMET Initiative [18]*Qualitative measures*. Satisfaction with the results of care, confidence as an active participant in healthcare decisions, confidence in healthcare providers.

The secondary outcomes are defined in detail in Additional file 1.

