## Conclusions

Maternal smoking rates are declining; however, smoking remains a significant risk factor for maternal and neonatal morbidity. A higher proportion of continued cigarette smoking is encountered in lower socioeconomic groups. Our previous research shows that the needs of pregnant smokers are largely unmet and under-resourced [19]. Smokers are a different population to non-smokers. They are more likely to be younger mothers, unemployed, with low educational attainment, a lack of social support, and increased incidence of mental illness [6]. Despite decades of research into smoking in pregnancy, the most effective antenatal model of care for smokers is still unclear. Additionally, while smokers are at significant risk of fetal growth restriction, specific recommendations for screening for growth restriction are absent.

Pregnant women are routinely offered specialised care and treatment for other risk-conferring conditions, for example, specialised clinics for diabetes, medical disorders, haematology, cardiology, and addiction. Our clinical trial aims to test a specific model of care for pregnant smokers, with smoking cessation as the primary outcome. We also expect that if a higher level of cessation is achieved, this will translate into improved secondary outcomes such as birth weight.

The main strength of this study is that it provides a smoking cessation intervention that is integral to the antenatal clinic model of care, meaning that women do not have to attend a separate appointment for smoking cessation advice. This should improve uptake of the smoking cessation intervention. There is a high rate of recidivism amongst quitters in pregnancy, with many women relapsing before the end of pregnancy and in the early postnatal period [20–22]. Less than a third of spontaneous quitters in pregnancy remain abstinent one year postpartum [22]. Women who are single and parous, who have a partner or household member who smokes, those with high depression scores, and those with a heavier smoking habit pre-pregnancy are most likely to relapse in the postpartum period [23, 24]. An additional strength of our trial is that the participants have a follow-up assessment of smoking status at 6 months after the birth.

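### The stated adjusted analysis includes no baseline smoking measure: a loss of efficiency, largest for cigarettes smoked and small for the primary outcome

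*Protocol article*

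**What the plan says.** The Statistical analysis section compares overall cessation rates by an unadjusted chi-square test at the 5% level. It then states that an ANCOVA "will be used to adjust for the stratification factors (age, parity, and history of fetal growth restriction". The list matches the Randomisation section, which describes "block randomisation (block size of 4) with stratification for age, parity, and history of previous fetal growth restriction". The text does not say which outcomes the ANCOVA covers.

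Four other places bear on the point:

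- **Population, Table 1:** entry requires "Smoking ≥1 cigarette daily", with no upper limit.
- **Intervention, Study protocol:** current smoking habits are recorded and "a measure of her level of addiction will be performed via the Fagerström test". This text opens by describing patients in the STOP clinic.
- **Primary outcome section:** the secondary smoking outcomes include "Number of cigarettes smoked" and cessation at 6 months postpartum.
- **Conclusions:** among other groups, "those with a heavier smoking habit pre-pregnancy are most likely to relapse". The sentence goes on to limit this to the period after birth.

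**The concern.** The article does more than leave adjustment to a later document. It commits to an adjusted analysis and lists the covariates, and none of them measures smoking. Women smoking one cigarette a day and heavy smokers enter on the same terms, and allocation is not stratified on intensity.

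If baseline smoking predicts later smoking, leaving it out wastes information that is cheap to collect. The loss matters most for number of cigarettes smoked, where the baseline value of the same quantity is the natural covariate. It also bears on cessation at 6 months postpartum, because the authors themselves name a heavier pre-pregnancy habit as a predictor of relapse after birth.

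Prespecification is also at stake. Patients and clinicians are not blinded, so a smoking covariate added after an imbalance had been seen would look data-driven.

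**Working it through.** **1. Does the plan's sample size depend on adjustment?**

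The Sample size justification aims to double the routine-care "cessation rate of 9% to give an intervention cessation rate of 18" per cent, and states: "Assuming a 5% level of statistical significance and 80% statistical power, the sample size is 225 per study arm". With p1 = 0.09, p2 = 0.18, mean 0.135, two-sided 5% and 80% power:

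n = [1.960 × √(2 × 0.135 × 0.865) + 0.842 × √(0.09 × 0.91 + 0.18 × 0.82)]² / 0.09²
= [1.960 × 0.4833 + 0.842 × 0.4791]² / 0.0081 = 1.8235 / 0.0081 = 225.1.

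Rounded up this is 226, against the stated 225. Power at 225 per arm is 80.0%. The design therefore stands on the unadjusted test.

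**2. Primary outcome: gain from a baseline smoking covariate.**

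The documents give no R² or odds ratio, so both are assumed.

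*By formula:* effective n = 225 / (1 − R²); the standard error is multiplied by √(1 − R²).

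| Assumed R² | Effective n | SE ratio | Power |
|---|---|---|---|
| 0 | 225.0 | 1.000 | 80.0% |
| 0.01 | 227.3 | 0.995 | 80.4% |
| 0.02 | 229.6 | 0.990 | 80.8% |
| 0.05 | 236.8 | 0.975 | 82.0% |
| 0.10 | 250.0 | 0.949 | 84.0% |
| 0.15 | 264.7 | 0.922 | 86.0% |

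*By simulation:* 6,000 trials per scenario, 225 per arm, one normal covariate, marginal rates held at 9% and 18%. The chi-square test is compared with a linear model with robust standard errors.

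| Assumed odds ratio per SD | Unadjusted power | Adjusted power |
|---|---|---|
| 1.0 | 81.1% | 80.8% |
| 1.5 | 80.9% | 81.6% |
| 2.0 | 81.0% | 82.8% |
| 2.5 | 81.5% | 84.0% |

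The gain for odds ratios of 1.5 to 2.5 is about 1 to 3 points. At 2.5 the simulated SD of the estimate falls from 0.0318 to 0.0308, an implied R² of 1 − (0.0308/0.0318)² = 0.06. The last two rows of the first table therefore assume a stronger predictor than any simulated here. Under no effect, the unadjusted test rejected in 4.7 to 5.1% of trials. The unadjusted estimate centred on the true difference in every scenario.

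**3. Chance imbalance.**

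The standard error of a between-arm difference in a standardised covariate is √(2/225) = 0.094 SD, so two standard errors are 0.19 SD. To first order, the shift in the risk difference is at most ln(OR) × 0.19 × the mean of 0.0819 and 0.1476 (= 0.115). For odds ratios of 1.5, 2.0 and 2.5 this is about 0.9, 1.5 and 2.0 percentage points. The standard error of the risk difference is √[(0.0819 + 0.1476)/225] = 3.2 points. Even an uncommon imbalance thus moves the estimate by about 0.3 to 0.6 of a standard error.

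**4. Number of cigarettes smoked.**

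Let r be the assumed correlation between baseline and follow-up, beyond what the stratification factors explain. ANCOVA on the baseline value multiplies the variance by 1 − r². If the outcome were instead analysed as change from baseline, with equal variances, the variance factor would be 2(1 − r).

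| Assumed r | ANCOVA factor 1 − r² | SE reduction vs follow-up value alone | Change-score factor 2(1 − r) |
|---|---|---|---|
| 0.3 | 0.91 | 5% | 1.40 |
| 0.5 | 0.75 | 13% | 1.00 |
| 0.7 | 0.51 | 29% | 0.60 |

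ANCOVA has the smallest variance in each row.

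**The case against.** The strongest reply is that nothing here is an error. The chi-square test is valid, adjusting for the stratification factors is proper practice, and the fix leaves the primary test unchanged. All of that stands. The finding concerns the supportive adjusted analysis and the secondary outcomes.

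A second reply is that the article does not say these are the only covariates. An analysis plan may add more, and Additional file 1 may define the cigarette outcome as a change from baseline. This is possible. But the text gives a covariate list, and that list has no smoking measure. A change score would still be less efficient than ANCOVA at the correlations shown.

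Four stronger readings are tempting, and the documents do not support them:

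- **That the omission biases the trial or leaves it exposed to imbalance.** Randomisation and the 5% test already allow for chance imbalance on average. The effect exists only conditionally on an observed imbalance, and step 3 shows that it is modest.
- **That the authors say heavy smokers are less likely to quit in pregnancy.** Their sentence concerns relapse after birth and the habit before pregnancy, not the count at booking. The primary outcome ends with the pregnancy.
- **That parity has little to do with smoking.** The same sentence lists parous women among those likely to relapse, so one of the planned covariates may itself be prognostic.
- **That the data already exist for every woman.** Eligibility shows only that a threshold was checked, not that a count was recorded. Smoking habits and the Fagerström score are described for STOP clinic patients. The assessment schedule (Fig. 3) is not shown, so collection in controls is neither confirmed nor excluded.

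**Conclusion.** The point holds as a recommendation on efficiency and prespecification. The stated adjusted analysis omits any baseline smoking measure, and a near-free gain in precision is forgone. It does not call the primary test into question.

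The gain is worthwhile for number of cigarettes smoked: a standard error about 5 to 29% lower for an assumed r of 0.3 to 0.7. It is small for validated quitting: about 1 to 3 power points for assumed odds ratios per SD of 1.5 to 2.5, and 0 to 6 points over an assumed R² of 0 to 0.15. For cessation at 6 months postpartum, the authors' own remark on relapse gives a reason to adjust but no effect size, so no figure can be put on it. Every size here rests on prognostic strengths that the documents do not supply.

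**What to change.** 1. Keep the unadjusted chi-square test as the primary analysis.
2. In the adjusted analysis already planned, add baseline cigarettes per day to age, parity and history of fetal growth restriction. For validated quit, use a logistic model and report a standardised risk difference.
3. Analyse number of cigarettes smoked by ANCOVA on its own baseline value.
4. Record the daily count for every woman, in the STOP group and both control groups, at the eligibility check before allocation.
5. Add the Fagerström score only if it is taken before allocation in all groups.

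The text change is a sentence or two, made before outcomes are seen by arm. The planned rates imply 225 × 0.09 + 225 × 0.18 = 20 + 41, or about 61 quits. With one term per factor, the model has five terms (arm, three stratification factors, cigarette count), about 12 quits per term.

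The real cost lies with women already in the trial, since recruitment began in February 2018. If counts were not recorded for controls randomised so far, they cannot be recovered as pre-allocation values, and the missingness would follow the arm. Simple imputation would then be unsafe. The sponsor should establish what was recorded in controls before amending, and state how missing baseline counts will be handled.
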